## Abstract

**Background:**

Prostate cancer (PrCa) is the second most common cancer in Ireland. Many men present with locally advanced or metastatic cancer for whom curative surgery is inappropriate. Advanced cancer patients are encouraged to remain physically active and therefore there is a need to investigate how patients with metastatic disease tolerate physical activity programmes. Physical activity reduces levels of systemic inflammatory mediators and so an aerobic exercise intervention may represent an accessible and cost-effective means of ameliorating the pro-inflammatory effects of obesity and subsequently decrease poor cancer-specific outcomes in this patient population. This study will assess the feasibility and safety of introducing a structured aerobic exercise intervention to an advanced cancer population. This study will also examine if the evasion of immune editing by circulating tumour cells (CTCs) is an exercise-modifiable mechanism in obese men with prostate cancer.

**Methods:**

This international multicentre prospective study will recruit men with metastatic prostate cancer. Participants will be recruited from centres in Dublin (Ireland) and London (UK). Participants will be divided into exposed and non-exposed groups based on body mass index (BMI) ≥ 25 kg/m^2^ and randomised to intervention and control groups. The exercise group will undertake a regular supervised aerobic exercise programme, whereas the control group will not. Exercise intensity will be prescribed based on a target heart rate monitored by a polar heart rate monitor. Blood samples will be taken at recruitment and at 3 and 6 months to examine the primary endpoint of platelet cloaking of CTCs. Participants will complete a detailed questionnaire to assess quality of life (QoL) and other parameters at each visit.

**Discussion:**

The overall aim of the ExPeCT trial is to examine the relationship between PrCa, exercise, obesity, and systemic inflammation, and to improve the overall QoL in men with advanced disease. Results will inform future work in this area examining biological markers of prognosis in advanced prostate cancer.

**Trial registration:**

Clinicaltrials.gov NLM identifier: NCT02453139. Registered on 12 May 2015. This document contains excerpts from the ExPeCT trial protocol Version 1.5, 28 July 2016.

## Background

### Prostate cancer

Prostate cancer (PrCa) is the most common cancer found in men in the developed world [1]. Many men present with locally advanced or metastatic cancer for whom curative surgery is inappropriate [2]. For these men, increases in progression-free and overall survival and quality of life (QoL) are the primary management objectives, and new therapies and assisting lifestyle alterations are increasingly needed.

### Metabolic syndrome and prostate cancer

Obesity, known to be associated with a pro-inflammatory, pro-thrombotic humoral milieu, confers a worse prognosis in PrCa. Between 1990 and 2002, Irish male obesity increased from 8% to 20%, with a further 47% of men overweight [3]. Metabolic syndrome (MS) is a constellation of risk factors for cardiovascular disease, with central adiposity and insulin resistance being the most important components. Male hypogonadism, due to androgen deprivation therapy (ADT)—the mainstay of treatment for locally advanced and metastatic PrCa—is an independent risk factor for the various components of MS [4–8]. MS is present in 50% of all men undergoing long-term ADT [9] and is associated with progression of PrCa [10]. This may explain the excess non-cancer mortality in this population [11].

MS is characterised by low-level chronic systemic inflammation. Increasing evidence suggests that substantial cross-talk occurs between molecular pathways involved in inflammation, coagulation, and obesity [12]. Elucidation of how these pathways interact with PrCa cells may shed light on why obesity disimproves PrCa prognosis.

### Circulating tumour cells and prostate cancer

Circulating tumour cells (CTCs) are identified in the blood in advanced cancer. Epithelial cells circulating in the blood of patients with carcinoma can be identified using various techniques including the ScreenCell® system (ScreenCell, Paris, France). Increasing evidence suggests that numbers of CTCs may have a prognostic role in advanced PrCa. A prospective study of castration-resistant PrCa found that ≥ 5 CTCs per 7.5 mL of blood correlated with a poor prognosis [13]. When a variety of clinical, serological, and pathological parameters were considered, the model best predictive of survival was based on baseline lactate dehydrogenase (LDH), baseline CTC count, and fold-change in CTC count at monthly intervals [14].

### Natural killer cells and obesity

Natural killer (NK) cell numbers in blood and in solid organs, as well as NK cell cytotoxicity and cytokine secretion, are known to be reduced in obesity [15]. In addition, obese people with hypertension, raised fasting glucose, and an unfavourable lipid profile have less NK cells than “metabolically healthy” obese patients. Obese subjects have lower numbers of hepatic NK cells and leptin receptor-positive cells compared with those of normal weight [16]. The NK cell fraction of white blood cells is sensitive to exercise [17], and five-fold increases in NK concentrations following acute exercise have been noted. Brief exercise upregulates molecular pathways in circulating NK cells associated with cancer and cell communication [18]. In healthy young men, hypoxic exercise training leads to enhanced in-vitro NK cell cytotoxicity [19].

### Interactions between platelets and circulating tumour cells

Despite the long-recognised association between cancer and thromboembolism, it has been unclear whether the thrombocytosis often seen in patients with metastases is a consequence or cause of widespread dissemination of the tumour. Accumulating evidence now shows that platelets support tumour metastasis by various mechanisms [20]. Platelets are involved in the arrest of CTCs in the vasculature and, through endothelial interactions, enable their extravasation. Platelets also secrete various pro-oncogenic factors including platelet-derived growth factor (PDGF) and vascular endothelial growth factor (VEGF), and mediate pro-survival signals in ovarian cancer cells [21].

Tumour cell-induced platelet aggregation correlates with metastatic potential, and may be due to “cloaking” of tumour cells by adherent platelets. The interaction between platelet cloaking of CTCs and tumour cell killing by NK cells is not completely understood. “Cloaking” of CTCs by adherent platelets may impede NK cell clearance of CTCs from the circulation, enhancing metastatic spread. Thrombocytopaenic mice exhibited reduced tumour metastatic burden when the tumour cells were NK cell sensitive, and in-vitro studies demonstrated reduced NK tumourilytic activity when platelets aggregated around tumour cells [22]. Platelets may enable evasion of immune editing by NK cells by conferring a “pseudonormal” phenotype on CTCs by encouraging high-level surface expression of normal major histocompatibility complex (MHC) class 1 antigen by the tumour cells [23].

In these pre-clinical studies there is an association between increased platelet-tumour cell interactions and endpoints of metastasis and death in animal models, but no clinical data exist as yet relating these interactions to outcomes in human disease. The current proposed study takes the current weight of evidence that platelet interactions are important in metastasis, and attempts to make the leap to demonstrate this in a clinical population. Platelet “cloaking” may be enhanced in obese patients due to the pro-inflammatory, pro-thrombotic state, and may be a mechanism for worse cancer-specific outcomes in this group.

### Prostate cancer and exercise

Several studies have shown that exercise may be protective against aggressive PrCa although there is no evidence that exercise protects against PrCa overall [24–27]. In PrCa patients there is solid evidence that exercise (especially group exercise) improves muscular and aerobic endurance, reduces fatigue, and improves overall quality of life [28].

Physical activity reduces levels of systemic inflammatory mediators [29], such as tumour necrosis factor (TNF)α, and so exercise may represent an accessible and cost-effective means of ameliorating the pro-inflammatory effects of obesity. This effect of physical activity depends on type, volume, and intensity, and does not depend directly on weight loss [30].

Obesity and its biochemical effects may be influenced by lifestyle changes such as exercise. As physical activity reduces levels of systemic inflammatory mediators, aerobic exercise may represent an accessible and cost-effective means of ameliorating the pro-inflammatory effects of obesity.

## Methods and design

### ExPeCT study objectives

The overarching hypothesis is that enhanced platelet cloaking of CTCs in obese men with prostate cancer, due to increased systemic inflammation, is a mechanism underlying worse prognosis of cancer in these patients.

The aim is to test the following four hypotheses, dividing the experimental and analytical work into four separate projects:Platelet cloaking of circulating PrCa tumour cells is more prominent in men with obesity than without.Regular exercise can ameliorate platelet cloaking.The degree of platelet cloaking varies with levels of systemic and primary tumour inflammation and coagulability.Expression of an obesity-associated lethality gene signature leads to variation in platelet cloaking.

### ExPeCT study design

This international multicentre prospective study will recruit men with metastatic PrCa from five Irish hospitals and one UK hospital. This study incorporates both an observational component, with exposed and non-exposed groups defined based on body mass index (BMI), and an exercise component, with randomization to exercise and control groups for a supervised exercise programme. Participants with metastatic prostate cancer will be recruited and divided into exposed (BMI ≥ 25 kg/m^2^) and non-exposed groups (BMI < 25 kg/m^2^). All exposed and non-exposed participants will be randomised to an exercise group or a control group, helping to minimise bias. The exercise group will participate in a 6-month exercise programme, comprising a weekly group exercise class and a home-based exercise programme. Participants will also be encouraged to complete activity diaries. From baseline (T0) to 3 months (T3), participants in the exercise arm will meet in small groups with a chartered physiotherapist for 1 h per week. At these sessions, participants will be educated about using the Polar heart rate monitors, prescribed their target exercise intensity, and complete a half-hour group aerobic exercise class. From T3 to 6 months (T6) continued aerobic exercise will be encouraged but classes will not be supervised by a chartered physiotherapist. All patients will be offered a personal exercise advice session at the study end to discuss long-term compliance to physical activity guidelines. Any patients demonstrating a need for further follow-up in relation to their physical activity levels will be advised to attend their general practitioner (GP) for a referral to the GP exercise scheme.

The study design consists of four main projects (Fig. 1):

**Fig. 1 Fig1:**
[figure not shown]
Schematic of the four projects involved in the ExPeCT trial. *BMI* body mass index, *CTC* circulating tumour cell, *H&E* haematoxylin and eosin, *NK* natural killer, *TNF* tumour necrosis factor

Project 1: CTCs will be enumerated in the T0 samples. Adherent platelets will be quantified and compared between the exposed and non-exposed groups, and correlated with clinicopathological parameters.Project 2: The exercise group will undertake a regular supervised aerobic exercise programme, whereas the control group will not. T3 and T6 blood samples will be assessed for CTC numbers and platelet cloaking. Changes will be compared with the T0 sample, and between exposed and non-exposed, and exercise and control groups. Participants will complete a detailed questionnaire to assess QoL and other parameters at each visit.Project 3: Blood samples will be assessed for NK cell number and activation, markers of systemic inflammation, adipokines, and serum factors related to platelet activation. The prostate needle core biopsies (NCBs) will be examined microscopically for atrophy and inflammation by morphology and immunohistochemistry, with particular reference to NK cells. All variables will be correlated with platelet cloaking.Project 4: NCBs will be assessed for expression of an obesity-associated lethality gene signature (whose genes are known to play a role in obesity or platelet aggregation and coagulation), and correlated with platelet cloaking of CTCs.

### ExPeCT participant selection criteria

#### Inclusion criteria

Written informed consent obtained before any study-related procedures.Aged ≥ 18 years and male.Histologically confirmed diagnosis of prostate adenocarcinoma.M1 metastatic disease as confirmed by computed tomography (CT)/magnetic resonance imaging (MRI) or by bone scan, excluding patients who only have nodal metastatic disease.Stable medical condition, including the absence of acute exacerbations of chronic illnesses, serious infections, or major surgery within 28 days prior to randomisation.Capable of participating safely in the proposed exercise as assessed and signed off by a treating physician involved in ExPeCT recruitment.

#### Exclusion criteria

Patients with a history of radical prostatectomy.Patients with other known malignancy (except non-melanoma skin cancers or fully excised carcinoma in situ at any site).

### Participant enrolment procedure

Potential patients will be enrolled to the study on the basis of the inclusion/exclusion criteria. Enrolment of patients will be undertaken by staff at the medical oncology clinics at each recruiting site as well as members of the ExPeCT research team who have been delegated this task by the principle investigator (PI) (Fig. 2). Any queries about eligibility will be addressed directly to the Chief Investigator. Informed consent will be obtained by clinic staff or a member of the ExPeCT research team according to the requirements of International Conference on Harmonisation-Good Clinical Practice (ICH-GCP).

**Fig. 2 Fig2:**
[figure not shown]
ExPeCT trial flowsheet

Upon registration of new participants, a signature confirming eligibility for the trial must be obtained from a treating physician involved in ExPeCT recruitment. Each registered patient will receive a unique participant identifier number (PIN). In order to ensure random allocation of participants to each study group, the computer programme Graphpad will be used to randomly assign a treatment group to each PIN. When issuing each PIN, two gatekeepers (1 in Ireland and 1 in the UK) will inform the research team of the treatment allocation of the participant. If a participant chooses to withdraw from the study, all data obtained up to the point of withdrawal will be carried forward unless requested otherwise.

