### Primary study endpoint

#### Platelet cloaking of circulating tumour cells

For each clinical review episode (at baseline and after 3 and 6 months), 12–16 mL of blood drawn from each patient into K_2_-EDTA tubes will be filtered by a ScreenCell® Cyto kit within 4 h. CTC enrichment depends on vacuum-assisted filtration through a microporous membrane filter to separate CTCs from other blood cells on the basis of size. Three to five filters will be generated for each participant, two of which will be stained with May-Grunwald Giemsa, followed by a broad-spectrum epithelial marker, and one to three reserved for platelet cloaking assays and other relevant markers. CTCs will be enumerated cytologically. The degree of platelet adhesion to CTCs will be assessed by immunohistochemistry. The number of CTCs with adherent platelets will be counted, and the approximate number of platelets adherent to each cell will be estimated.

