### Data management

The ExPeCT research team will be the only people with access to the data collected in the course of this project. Data analysis will be performed at St. James’s Hospital by the in-house bioinformatics team and other members of the ExPeCT research team. At the end of the study period, when all analysis is complete, data will be retained by the ExPeCT research team. Data will be securely stored for up to 10 years with the option of requesting ethical permission for a prolonged storage time.

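### Allocation is disclosed to the whole research team and no masked reading of the subjective primary endpoint is stated, so reader expectation could materially bias the randomised comparison of cloaking over time

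*Protocol article*

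**What the plan says.** Participant enrolment procedure (the text below Fig. 2): when each participant number is issued, two gatekeepers, one in Ireland and one in the UK, "will inform the research team of the treatment allocation of the participant". The sentence does not divide the team by role.

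Primary study endpoint: filters are stained and read under the microscope. "CTCs will be enumerated cytologically", CTCs with adherent platelets are counted, and "the approximate number of platelets adherent to each cell will be estimated". The abstract confirms the endpoint and its timing: "Blood samples will be taken at recruitment and at 3 and 6 months to examine the primary endpoint of platelet cloaking of CTCs".

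Data management: "The ExPeCT research team will be the only people with access to the data collected in the course of this project". Analysis is done "by the in-house bioinformatics team and other members of the ExPeCT research team".

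ExPeCT study design: men in both BMI groups "will be randomised to an exercise group or a control group, helping to minimise bias". This is the only bias control that the article names. It does not mention masked reading, coded filters, a second reader or reader agreement.

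**The concern.** Randomisation makes the arms comparable at entry. It does not protect an outcome scored by eye by someone who knows the arm. Deciding whether a cell is a CTC, whether platelets adhere to it and roughly how many involves judgement at each step, and the study hypothesis (exercise reduces cloaking) tells an informed reader which way to expect the answer. The intention-to-treat mixed models planned for Project 2 do not remove measurement error that differs by arm.

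As written, the text lets the same people know the allocation, score the filters and analyse the results. Team members also take part in enrolment and, from T3 to T6, telephone exercise participants weekly. The article separates none of these roles from slide reading. What is at stake is the randomised comparison of the primary endpoint.

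**Working it through.** **Inputs**
- Sample size section: 200 men, 100 per arm; SD of cloaking 2% to 10%; detectable two-group difference 0.79% to 3.9%.
- Assumed, because the article states neither: two-sided alpha 0.05 and 80% power.
- Assumed, because the article gives no reader error: a differential reading shift b between arms. The illustration uses b = 0.5 percentage points, equivalent to one CTC in 200 (1/200 = 0.5%) scored differently in one arm on average.

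**Step 1: reproduce the plan's figure.** Detectable difference = SD × (1.960 + 0.842) × √(2/100).
- SD 2%: 2 × 2.802 × 0.1414 = 0.79, as stated.
- SD 10%: 10 × 2.802 × 0.1414 = 3.96, against 3.9 stated. The stated value looks truncated; power at 3.9 is 78.7%.

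The assumed alpha and power therefore fit the plan's own numbers.

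**Step 2: size of the shift against the detectable difference.**
- SD 2%: 0.5/0.79 = 63%.
- SD 10%: 0.5/3.9 = 13%.

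**Step 3: false-positive rate with no true effect.** SE = SD × √(2/100). Rate = 1 − Φ(1.96 − b/SE) + Φ(−1.96 − b/SE).
- SD 2%: SE = 0.283, b/SE = 1.77; 1 − Φ(0.19) + Φ(−3.73) ≈ 0.42.
- SD 10%: SE = 1.414, b/SE = 0.354; 1 − Φ(1.61) + Φ(−2.31) ≈ 0.054 + 0.010 = 0.064.

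**Step 4: general scale.** With the shift written as a fraction of the detectable difference, the result does not depend on the SD. The last column applies when the shift runs against a true effect equal to the detectable difference.

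| Shift / detectable difference | Points at SD 2% | Points at SD 10% | False-positive rate | Power left |
|---|---|---|---|---|
| 0 | 0 | 0 | 5% | 80% |
| 25% | 0.20 | 0.99 | 10.8% | 55.6% |
| 50% | 0.40 | 1.98 | 28.8% | 28.8% |
| 100% | 0.79 | 3.96 | 80% | 5% |

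These are simple two-group calculations at one time point. The planned mixed model would have somewhat different precision, but a shift that differs by arm passes into its estimate in the same way.

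**The case against.** The strongest reply is that the article never says who reads the filters. The endpoint section is in the passive voice, and the research team is a broad label that includes people who must know the arm to run classes and issue heart rate monitors. A reader might infer that the microscopist is told the allocation, or that nothing masks the slides. Neither is stated. The article describes itself as excerpts of protocol version 1.5, slide labelling is not described either way, and two relevant figures are not shown. The data-access sentence concerns confidentiality, and the remark about minimising bias describes randomisation without claiming to protect the reading.

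Three further limits stand. Disclosure of arm cannot bias a baseline comparison by BMI, and no sentence says that readers know BMI. The 0.5-point shift has no source in the document and would have to occur on average across a whole arm; at SD 10% it does little. The 2% reference level comes from ovarian cancer cell lines, while the Project 4 categories cut cloaking at 25% and 75%, so expressing a shift as a share of that 2% would mislead.

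These points narrow the concern but do not remove it. It does not rest on silence alone: the disclosure to the whole team is a stated rule, nothing exempts the slide readers from it, and the endpoint is described as a human count with an approximate component.

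**Conclusion.** The concern holds for Project 2. Followed as written, the article permits the primary endpoint to be read with knowledge of arm, and that could materially bias the randomised comparison of cloaking over time. It bears less on the T0 BMI comparison.

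Its size cannot be fixed from the document. Under the assumed 0.5-point shift, the false-positive rate is about 42% at SD 2% and about 6.4% at SD 10% (100 per arm, two-sided 5%). A reader might go further and infer that expectation could create or hide the entire effect. That would need a differential shift as large as the detectable difference (0.79 points at SD 2%, 3.96 at SD 10%), and nothing in the article supports an error of that size. The finding also depends on the full protocol not already masking the readers.

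**What to change.** 1. Limit the allocation disclosure to staff who deliver the exercise programme or manage visits.
2. Have the existing gatekeepers give each filter a code that carries no participant number, arm, BMI or visit.
3. Read filters in batches that mix arms and visits, and lock the reads before linking codes to allocation.
4. Flag reads already made unmasked and examine their influence in a sensitivity analysis. The Trial status section describes data collection as ongoing, so later reads can still be masked.
5. If the full protocol already masks the readers, say so in the article and correct the disclosure sentence to match.

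The cost is small: coding three to five filters per man per visit across two countries, and reading in batches rather than as samples arrive. No participant procedure changes.
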